### Outcome measurements: secondary endpoints

Secondary outcomes include both subjective and objective outcomes. Subjective outcomes include symptom improvements measured by the NYHA Functional Classification [38], symptom improvements evaluated by the TEAM pattern identification questionnaire [39–43] and quality of life measured by the EuroQol Five Dimensions Questionnaire (EQ-5D) [44] and the Minnesota Living with Heart Failure Questionnaire (MLHFQ) [45]. Objective outcomes include routine blood tests (renal function and electrolyte imbalance), cardiac biomarkers, NT-pro BNP, hs-CRP, cardiac function measured by echocardiography, HRV, and MACE.

#### Heart failure symptom improvement (NYHA)

The NYHA Functional Classification will be used to assess symptoms of improvement [38]. It categorizes the patient into one of four levels according to limitations during physical activity.Class I:
*“No limitation of physical activity. Ordinary physical activity does not cause undue fatigue, palpitation, dyspnea (shortness of breath).”*
Class II:
*“Slight limitation of physical activity. Comfortable at rest. Ordinary physical activity results in fatigue, palpitation, dyspnea (shortness of breath).”*
Class III:
*“Marked limitation of physical activity. Comfortable at rest. Less than ordinary activity causes fatigue, palpitation, or dyspnea.”*
Class IV:
*“Unable to carry on any physical activity without discomfort. Symptoms of heart failure at rest. If any physical activity is undertaken, discomfort increases.”*

#### Pattern identification (syndrome differentiation) questionnaire

A pattern identification questionnaire according to TEAM theory will be assessed on Day 1 and Visit 2. Food retention (accumulation) (食積) [40], phlegm (痰飮) [39], blood stasis (瘀血) [41], seven-emotion impairment (七情) [43], and fatigue due to overexertion (勞倦) [42] will be diagnosed by KMDs with a validated pattern identification questionnaire. Each questionnaire has a total score and a cut-off value. The change in value from Day 1 to Visit 2 will be compared. The proportion of participants who have certain TEAM syndrome will also be compared.

#### Quality of life

EQ-5D is a self-reported standardized and validated questionnaire that assess QOL using general questions related to health status [44]. We will use the validated Korean version of EQ-5D [46]. MLHFQ is a HF-specific QOL questionnaire [45]. It sensitively assesses change before and after treatment. The changes in value from the baseline of the two groups will be compared.

#### Routine blood tests

Routine blood tests will be performed to evaluate renal function, electrolyte imbalance, and safety. A complete blood cell count, blood urea nitrogen, creatinine, electrolytes (Na, K, Cl), total bilirubin, glucose, total protein, albumin, aspartate aminotransferase, and alanine aminotransferase will be measured.

#### Cardiac biomarkers

Atrial natriuretic peptide, ST2, catecholamine, vasoactive intestinal peptide, IL-6, and vascular adhesion protein-1 will be measured. These cardiac biomarkers were selected according to a consensus among the research team members and previous research [47–55]. The changes in value from the baseline of the two groups will be compared.

#### NT-pro BNP

Both BNP and NT-pro BNP are useful natriuretic peptides that can diagnose acute decompensated HF [56] and predict prognosis [57]. We adopted NT-pro BNP because it has greater prognostic value than BNP [58]. The group with an NT-pro BNP level higher than the median has increased mortality compared to the group with levels lower than median. The change in value of NT-pro BNP from the baseline will be compared.

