#### Cardiac function

Echocardiography is a helpful, non-invasive assessment tool of ventricular function and hemodynamics in HF patients. Ejection fraction (%), the ratio between early mitral inflow velocity and mitral annular early diastolic velocity (E/e’ ratio), left ventricular fractional shortening (%), left ventricular end diastolic diameter (mm), and left ventricular end systolic diameter (mm) will be evaluated by echocardiography to assess cardiac function. Follow-up echocardiography will be assessed 180 days after discharge. The changes in value from the baseline between the two groups will be compared.

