#### HRV

HRV reflects ANS status [12]. As sympathetic dominance is an important pathophysiology of HF, HRV is a known important prognostic factor of HF [13, 14]. A Holter monitoring device will measure 24-h heart rate variability. The changes in value from baseline between the two groups will be compared.

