### Sample size calculation

The primary outcome of our study is the total diuretic doses of the treatment and control groups during hospitalization. In a previous study about the effect of the adenosine A1-receptor antagonist (rolofylline) in acute decompensated HF and renal impairment patients, the mean and standard deviation of total diuretic doses were reported [25]. In the trial, doses of 0, 2.5, 15, 30, and 60 mg of rolofylline were used. Our trial offers conventional treatments to both groups and compares the diuretic doses of the real acupuncture and sham acupuncture groups. Therefore, through consensus of the research team members, we assume the effect of real and sham acupuncture on the diuretics doses will be similar to 15 mg and 30 mg rolofylline, respectively. In the study, the cumulative dose of furosemide usage during hospitalization in the group receiving 30 mg of rolofylline was 223 ± 26 mg. In the group receiving 15 mg, it was reported to be 256 ± 39 mg. In a superiority test, with 80% of power (1-β = 0.8) and 5% of significance level (α = 0.05) in a two-sided *t*-test, calculated sample size of each group was 17 participants. After determining that the dropout rate will be approximately 20%, the sample size of each group was increased to 22; and the total sample size was 44. Sample size was calculated using G-power 3.1 software (Heinrich-Heine-Universität, Düsseldorf, Germany).

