### Statistical analysis

The primary outcome of our study is the cumulative amount of diuretic administered to each group. After a normality test, the total amount will be compared by an independent *t*-test (parametric) or a Mann-Whitney U test (non-parametric) according to the normality of the data. If the baseline characteristic is significantly different between the two groups, an analysis of covariance (ANCOVA) will be used to adjust the baseline difference. In baseline characteristics and secondary outcome analysis, binary outcomes will be compared by a chi-square test or Fisher’s exact test. Continuous outcomes will be compared by an independent *t*-test (parametric) or Mann-Whitney U test (non-parametric). MACE will be also be analyzed using the survival analysis method. Statistical analysis will be performed using the R package by a blinded statistician. A 5% significance level will be used. Missing values will be replaced by the last observation carried forward method. If there are more than 20% of drop out participants, sensitivity analysis will be conducted including the data.

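### Continuous secondary outcomes are tested as change from baseline without routine baseline adjustment: valid, but it gives up precision that could be had free

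*Protocol article*

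**What the plan says.** The protocol article names change from baseline as the quantity compared for nearly every continuous secondary outcome:

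- NT-pro BNP: "The change in value of NT-pro BNP from the baseline will be compared".
- Cardiac biomarkers: "The changes in value from the baseline of the two groups will be compared". The Quality of life section says the same for EQ-5D and MLHFQ.
- Cardiac function: "The changes in value from the baseline between the two groups will be compared". The hs-CRP section uses the same sentence.
- HRV: "The changes in value from baseline between the two groups will be compared".
- The pattern identification section compares the change in score from Day 1 to Visit 2.

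The test is given under Statistical analysis: "Continuous outcomes will be compared by an independent" t-test if parametric, or by a Mann-Whitney U test if not. Baseline adjustment appears once in that section, directly after the primary-outcome test: "If the baseline characteristic is significantly different between the two groups, an analysis of covariance (ANCOVA) will be used to adjust the baseline difference".

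Table 1 schedules a baseline value, at screening or on Day 1, for each of these measures.

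**The concern.** Subtracting the baseline fixes its coefficient at 1. ANCOVA estimates that coefficient from the data, so it generally has a smaller error variance, and it also corrects for chance imbalance in the outcome's own baseline. The trial has 22 patients per arm, and Objectives lists these outcomes among the measures of effectiveness, so avoidable loss of precision matters.

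The biomarkers raise a second issue. The NT-pro BNP entry criterion has a floor of 600 pg/mL (or BNP above 150 pg/mL) and no upper limit, so starting values may differ widely between patients. If treatment acts proportionally, absolute change depends strongly on where a patient started. That variation hides a treatment effect.

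**Working it through.** **Trial size.** Sample size calculation gives 223 ± 26 mg and 256 ± 39 mg, 80% power, and "5% of significance level (α = 0.05) in a two-sided *t*-test, calculated sample size of each group was 17 participants".

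- Difference = 256 − 223 = 33. Pooled SD = √((26² + 39²)/2) = √1098.5 = 33.14. d = 33/33.14 = 0.996.
- Power from the noncentral t distribution is 77.8% at 16 per group and 80.4% at 17, so 17 reproduces.
- With 20% dropout, 17/0.8 = 21.25, rounded up to 22. This also reproduces.

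The secondary outcomes will therefore have between 17 (completers) and 22 (all randomised) per arm.

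**Precision, general case.** Let sb and sf be the baseline and follow-up SDs and r their correlation.

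- Var(change) = sb² + sf² − 2·r·sb·sf
- Var(ANCOVA) = sf²·(1 − r²)
- Difference = sb² − 2·r·sb·sf + r²·sf² = (sb − r·sf)²

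The difference is never negative. It is zero only when r·sf = sb, for example r = 0.8 with sf = 1.25·sb.

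**Precision, equal SDs (assumed).** The ratio Var(ANCOVA)/Var(change) = (1 − r²)/(2(1 − r)) = (1 + r)/2. The documents give no r, so these values are assumptions. An ANCOVA with n per arm is worth n divided by the ratio on change scores.

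| assumed r | ratio | 17 per arm worth | 22 per arm worth |
|---|---|---|---|
| 0.3 | 0.65 | 26.2 | 33.8 |
| 0.5 | 0.75 | 22.7 | 29.3 |
| 0.7 | 0.85 | 20.0 | 25.9 |

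Estimating the slope multiplies the ANCOVA variance by about 1 + 1/(2n − 4), which is 1.033 at n = 17 and 1.025 at n = 22. At n = 22 the ratios become about 0.67, 0.77 and 0.87. At r = 0.5 the equivalents become 17/0.775 = 21.9 and 22/0.769 = 28.6.

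**Precision, unequal SDs.** If the follow-up SD is 0.7 of the baseline SD, Var(change)/Var(ANCOVA) is 2.0 to 2.4 for r from 0.3 to 0.8. The equal-SD ratios are illustrations, not bounds.

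**Conditional ANCOVA.** At the 5% level, randomised groups differ significantly on a given outcome's own baseline about 5% of the time. In the other 95% or so, the stated rule leaves that outcome unadjusted for its own baseline.

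**Skewed biomarkers.** A simulation (4,000 trials per setting) assumed a log-normal marker with log-SD 0.8 to 1.0, r = 0.5 to 0.8, a true treatment ratio of 0.5 and a common fall in both arms. The planned route was taken as a Shapiro-Wilk test in each arm, then a t-test or Mann-Whitney test on absolute change.

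| analysis | power, 17 per arm | power, 22 per arm |
|---|---|---|
| t-test, absolute change | 11–23% | 14–28% |
| planned route | 19–36% | 24–43% |
| t-test, log change | 50–97% | 60–99% |
| ANCOVA, log scale | 60–98% | 73–99.8% |

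With no treatment effect (22 per arm, log-SD 1.0, r = 0.7), the planned route rejected in 5.3% of trials. Most of the gain for a skewed marker comes from the log scale, and baseline adjustment adds to it.

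**The case against.** Several stronger readings are tempting, and the document does not support them.

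- *The analysis is biased or invalid.* It is not. Comparing change scores between randomised arms is unbiased, and the simulated type I error was near 5%.
- *The plan never adjusts for baseline.* It does, conditionally. The rule is weak because the gain in precision comes from the correlation between baseline and follow-up, not from a significant imbalance. It must still be acknowledged.
- *A few extreme patients will drive the biomarker results.* That fits only the t-test branch. Strongly skewed changes would probably fail a normality check and go to Mann-Whitney, where an extreme value counts only by its rank. What remains is lost power: ranks of absolute change still mix treatment effect with starting level.
- *ANCOVA gains unless r = 1.* That holds only for equal SDs. The general condition for no gain is r·sf = sb.
- *The article commits to absolute pg/mL.* It speaks only of change in value and names no scale. A log transformation may be in an analysis plan that is not shown, so its absence here is not an error. The skewness part of the point applies only if change is taken on the absolute scale.

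It is also fair to say that the trial is powered for diuretic dose alone, and that the Discussion rests its therapeutic claim on reduced diuretic use. That limits the importance of this point but does not remove it. The article does state both the quantity compared and the test, and a better choice is available from data already scheduled.

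**Conclusion.** The point holds as one of efficiency in the continuous secondary outcomes. With equal SDs and r from 0.3 to 0.7, both assumed, ANCOVA variance is 0.65 to 0.85 of the change-score variance. Confidence intervals would be about 19% to 8% narrower (√0.65 = 0.81, √0.85 = 0.92), before the small cost of the slope. The direction does not depend on these assumptions, apart from that slope cost and the special case r·sf = sb; the size does. The power contrast for skewed biomarkers is larger but rests on an assumed log-normal marker and a halving effect, a setting that favours log-scale analysis. It should be read as an illustration.

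**What to change.** In Statistical analysis, remove the significance-test trigger for these outcomes. State that the follow-up value of every continuous secondary outcome will be analysed by ANCOVA with its own baseline as covariate, whatever the baseline comparison shows. For NT-pro BNP, hs-CRP and other skewed biomarkers, use the log scale and report the ratio of geometric means. On any one scale, a model for change with baseline as covariate gives the same treatment estimate, so change can still be the quantity described.

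A repeated-measures model for NT-pro BNP and hs-CRP at Day 5 and Visit 2 is optional. If it is used for hs-CRP, the hs-CRP section, which mentions only screening and discharge, should first be reconciled with Table 1, which also lists Visit 2.

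The cost is an amendment of wording. Under Ethics approval and registration, it would be reported to the IRB and announced to participants and investigators. It should be made before anyone sees outcomes by arm. No extra patients, visits or assays are needed.

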#### hs-CRP

In HF, chronic inflammation status is related to the pathophysiology of the disease [59]. Patients with more severe HF symptoms have a higher hs-CRP level [60]. On screening and discharge days, hs-CRP will be measured. The changes in value from the baseline between the two groups will be compared.

#### Cardiac function

Echocardiography is a helpful, non-invasive assessment tool of ventricular function and hemodynamics in HF patients. Ejection fraction (%), the ratio between early mitral inflow velocity and mitral annular early diastolic velocity (E/e’ ratio), left ventricular fractional shortening (%), left ventricular end diastolic diameter (mm), and left ventricular end systolic diameter (mm) will be evaluated by echocardiography to assess cardiac function. Follow-up echocardiography will be assessed 180 days after discharge. The changes in value from the baseline between the two groups will be compared.

#### HRV

HRV reflects ANS status [12]. As sympathetic dominance is an important pathophysiology of HF, HRV is a known important prognostic factor of HF [13, 14]. A Holter monitoring device will measure 24-h heart rate variability. The changes in value from baseline between the two groups will be compared.

#### MACE

Mortality due to heart and kidney problems and the readmission rate between the two groups will be compared until 180 days after discharge.

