**Methods:**

This protocol is for a randomized, sham controlled, patient- and assessor-blinded, parallel group, single center clinical trial that can overcome the limitations of previous trials examining acupuncture and heart failure. Forty-four acute decompensated heart failure patients admitted to the cardiology ward will be randomly assigned into the electroacupuncture treatment group (*n* = 22) or the sham electroacupuncture control group (*n* = 22). Participants will receive electroacupuncture treatment for 5 days of their hospital stay. The primary outcome of this study is the difference in total diuretic dose between the two groups during hospitalization. On the day of discharge, follow-up heart rate variability, routine blood tests, cardiac biomarkers, high-sensitivity C-reactive protein (hs-CRP) level, and N-terminal pro b-type natriuretic peptide (NT-pro BNP) level will be assessed. Four weeks after discharge, hs-CRP, NT-pro BNP, heart failure symptoms, quality of life, and a pattern identification questionnaire will be used for follow-up analysis. Six months after discharge, major cardiac adverse events and cardiac function measured by echocardiography will be assessed. Adverse events will be recorded during every visit.

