According to the implications for future clinical trials of the previous review, our study team planned an electroacupuncture clinical trial for acute decompensated HF patients that could overcome previous limitations. First, our primary outcome was the total diuretic dose administered during hospitalization, which has been recorded in several acute HF clinical trials [25–28]. As acupuncture treatment is an adjunctive treatment in cases of HF, our research team concluded that reducing the total dose and the adverse effects of the diuretics through acupuncture treatment is meaningful. Second, we included several important outcomes, such as mortality, MACE, NYHA Functional Classification, cardiac biomarkers, NT-pro BNP, and cardiac function measured by echocardiography. Third, we adapted the electroacupuncture protocol. In addition, we adapted a Park Sham Device (PSD; Acuprime, Exeter, UK), a validated sham acupuncture device [29], to maintain blindness and non-biased measurement of subjective outcomes. Last, we will follow the participants until 6 months after discharge to assess the long-term effects of acupuncture treatment in acute HF.

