### Intervention

#### Study flow

If the participants voluntarily sign informed consent during admission to the cardiology ward, participants will be screened according to inclusion and exclusion criteria on the screening day. After the subject fulfills the criteria, the basic characteristics and prognostic factors of each participant will be evaluated. The subjects will be randomized into an intervention and a control group with a 1:1 allocation ratio on the same day; the screening day and Day 1 will usually be the same day. From Day 1 to Day 5, the participants will receive electroacupuncture treatment or sham electroacupuncture treatment once a day for consecutive 5 days according to their allocated group. After discharge, participants will visit KHMC three times. Visit (V1) will be 7 days after discharge. Visit 2 (V2) will be 28 days after discharge. Visit 3 (V3) will be 180 days after discharge. On the day discharge (Day 5) and V2, blood tests, quality of life (QOL), and a pattern identification questionnaire according to traditional East Asian medicine (TEAM) theory will be evaluated. On V3, cardiac function and MACE will be evaluated by echocardiography (Table 1). Participants will be withdrawn from the study if they 1) re-admit to hospital related to cardiac or kidney dysfunction 2) withdraw of consent by participants 3) worsening cardiac function 4) the principle investigator judged that participants can not continue the research.

**Table 1 Tab1:** Study schedule

Study period	Screening visit	Acupuncture treatment period					Follow-up period		
Visit	Screening	D1	D2	D3	D4	D5	V1	V2	V3
Informed consent	X								
Demographics and history collection	X								
Inclusion and exclusion criteria	X								
Randomization		X							
Physical examination and vital signs check	X	X	X	X	X	X	X	X	X
Body weight	X	X	X	X	X	X	X	X	X
Symptoms check (NYHA Functional Class)	X	X	X	X	X	X	X	X	X
Adverse events	X	X	X	X	X	X	X	X	X
Concomitant medication check	X	X	X	X	X	X	X	X	X
Routine blood test^a^	X		X			X		X	X
NT-pro BNP, hs-CRP	X					X		X	
Cardiac biomarkers^b^		X				X			
Cardiac function (echocardiography)	X								X
Electrocardiogram and HRV		X				X			
QOL and symptom questionnaire^c^		X						X	
Credibility and AES		X				X			
Blinding test		X				X			
Acupuncture treatment		X	X	X	X	X			

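### The death part of MACE covers only heart and kidney causes, no all-cause mortality endpoint is listed, and the only time anchor is discharge, which follows randomisation

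*Protocol article*

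**What the plan says.** All references are to the protocol article.

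- **MACE section:** "Mortality due to heart and kidney problems and the readmission rate between the two groups will be compared until 180 days after discharge". This gives two components, cause-restricted death and readmission, and an end to the window. It gives no start.
- **Background:** the authors say "we included several important outcomes, such as mortality, MACE, NYHA Functional Classification" and further measures. The preceding paragraph, which reports what an earlier systematic review recommended, also lists mortality and MACE as separate items.
- **Objectives and secondary endpoints:** both name MACE and neither names mortality. The list of objective outcomes ends with "cardiac function measured by echocardiography, HRV, and MACE".
- **Abstract (Methods) and Study flow:** "Six months after discharge, major cardiac adverse events and cardiac function measured by echocardiography will be assessed", and "Visit 3 (V3) will be 180 days after discharge". Randomisation is on Day 1.
- **Statistical analysis:** "MACE will be also be analyzed using the survival analysis method". Nothing is said about the time origin or about deaths outside the definition.
- **Study flow, withdrawal:** one reason for withdrawal is that participants "re-admit to hospital related to cardiac or kidney dysfunction". Worsening cardiac function is another.

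**The concern.** There are three linked weaknesses.

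1. Mortality is announced as an included outcome, but the endpoint list contains only MACE, and MACE admits only heart and kidney deaths. No between-group comparison of death from any cause is planned.
2. The follow-up limit is counted from discharge, an event after randomisation. All five treatment sessions are given in hospital. A patient who dies there has no discharge date, so the text does not say how that patient enters the comparison.
3. A death from another cause prevents any later readmission or cardiac death. The planned survival analysis does not say how such a death is handled, so the choice could be made after the data are seen.

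Withdrawal on readmission adds to this. A MACE event can end a patient's follow-up, and a death after it may never be recorded.

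What is at stake is how a clinically important secondary outcome reads. In a trial this small, one or two patients placed differently can change the impression it gives.

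**Working it through.** **The plan's only sample-size figure.** It concerns the primary outcome, not MACE, and is checked here only to fix the arm size. The Sample size calculation section gives 256 ± 39 mg and 223 ± 26 mg, 80% power and two-sided α = 0.05.

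- Difference: 256 − 223 = 33 mg
- Pooled SD: √((26² + 39²)/2) = 33.14 mg
- Standardised difference: 33/33.14 = 0.996
- Exact two-sample t-test: 16.85, so 17 per group, with power 0.804
- Dropout: 17/(1 − 0.20) = 21.25, so 22 per group and 44 in total

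The stated figures reproduce. No sample size or event rate is given for MACE.

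**Which events have a stated place in the MACE comparison**

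| Event | Under the text as written |
|---|---|
| Readmission after discharge, any cause | Counted; the MACE section sets no cause restriction |
| Heart or kidney death within 180 days of discharge | Counted, if still observed after any withdrawal |
| Other-cause death after discharge | Outside the endpoint; handling in the survival analysis not stated |
| Heart or kidney death before discharge | Cause fits, but there is no discharge date and no start of the window; undefined |
| Other-cause death before discharge | Outside the endpoint and undefined in time |

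**Withdrawal set beside the definition.** Take a patient readmitted for heart failure on day 30 and withdrawn under Study flow, who dies of heart failure on day 90. The readmission is known. The death belongs to the endpoint, but the document does not promise follow-up that would find it. A patient withdrawn for worsening cardiac function without readmission is more awkward still: follow-up may stop before any MACE event, at a time of raised risk.

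**Scale.** One patient in one arm is 1/22 = 4.5 percentage points, and two are 2/22 = 9.1.

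The documents give no in-hospital mortality. Purely as an illustration, with assumed rates p:

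| Assumed p | Expected deaths, 44p | Chance of at least one, 1 − (1 − p)⁴⁴ |
|---|---|---|
| 2% | 0.9 | 59% |
| 4% | 1.8 | 83% |
| 7% | 3.1 | 96% |

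The exclusion criteria remove many of the sickest patients, so the lower end is the more plausible. These rates cannot be used to size the effect.

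**What MACE can show at this size.** The Schoenfeld formula for events at 80% power and two-sided 0.05, with an assumed hazard ratio of 0.5, gives 4 × (1.960 + 0.842)²/(ln 0.5)² = 31.4/0.480 ≈ 65.4, so 66 events. That exceeds the 44 patients randomised. With 20 events, power is Φ(0.693 × √20/2 − 1.960) = Φ(−0.41) = 0.34. The analysis is descriptive under either definition.

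**The case against.** The strongest reply is that this is an article-length protocol. Time origin, censoring and competing events are commonly left to an analysis plan, and a cause-specific death component is a legitimate choice for a cardiac endpoint. Both statements are fair. Silence on technique alone would not be a finding. What stands is what the article does state: a list of included outcomes that its endpoint list does not match, a time limit that cannot be computed for every randomised patient, and a withdrawal rule that works against its own endpoint.

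The Background phrase is only an illustrative list and does not say all-cause. That is true, and mortality does appear inside MACE. But the phrase sets mortality beside MACE as a separate item, and no separate item follows.

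A reader might also infer several stronger things that the documents do not support:

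- **That in-hospital deaths are excluded and the comparison is conditional on surviving to discharge.** The wording fixes only the end of the window. A start at randomisation is compatible with it. These deaths are undefined, not excluded.
- **That other-cause deaths must be censored.** Survival methods include competing-risk approaches, and the Statistical analysis section rules none out.
- **That such deaths are lost to the trial.** All adverse events are recorded at every visit, so deaths should surface under safety. That is a record, however, not a stated group comparison.
- **That this is the main safety outcome.** MACE is one of many secondary outcomes, and safety has its own section.
- **That a treatment effect on length of stay seriously distorts the time scale.** Table 1 equates Day 5 with discharge. Differences of a few days would be small against 180 days and a visit window of ±14 days.

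**Conclusion.** The point holds in a limited form. All-cause death has no place among the listed endpoints despite the Background statement. Other-cause deaths fall outside the survival endpoint without a stated rule. A patient who dies before discharge has no defined 180-day limit. Separately, the withdrawal rule in Study flow and the MACE definition must be reconciled, because an event that counts towards MACE can end the follow-up needed to complete it.

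The effect cannot be sized from the documents. What can be said is that each affected patient is worth 4.5 percentage points in an arm of 22, and that MACE is descriptive with 44 patients. The primary outcome and its sample size are untouched. The documents do not show that the randomised comparison is lost. They do leave room for a better definition at low cost, and it should be settled before the data are examined.

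**What to change.** 1. Define MACE as time from randomisation to the first of death from any cause or readmission, in all randomised patients, followed through V3. Deaths before discharge then count as events on the day they occur.
2. Report heart and kidney deaths as a component, and keep the cause-specific version as a supporting analysis with the handling of other-cause deaths stated.
3. List all-cause mortality as a descriptive secondary outcome, so that the Background, Objectives, secondary endpoint list and MACE section agree.
4. Reconcile the withdrawal criteria in Study flow with the MACE section, so that withdrawal on cardiac or renal readmission or worsening cardiac function does not end collection of vital status and readmissions through V3.

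**Cost.** Items 1 to 3 are changes of wording and analysis. Item 4 is more than wording: vital status and readmissions must be obtained after withdrawal, within the limits of each participant's consent. A time-to-first-event composite is less exposed to withdrawal on readmission, because the readmission has already been counted, but all-cause mortality is not. The other downside is that a few deaths unrelated to the heart or kidneys will enter the composite, which is why the cause-specific version is kept alongside it.
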